### Data collection

3.8

Data collected in the study are listed in Table 1. Electronic data will be stored and saved on a pass-word-protected computer. Hard (paper) copies of the consent form, questionnaire, and data sheets from the ultrasound examination will be stored in a locked filing cabinet in the principal researcher's computer. Downloaded from and members of the research team will be given access to the data.

**Table 1 T1:**
[figure not shown]
Data collected in the study.

### Sample size and study power

3.9

Optimal sample size has been evaluated based on a statistical power of 80% and a significance level of 0.05 (two-tailed). According to the previous study, in obese surgical patients, an incidence of difficult intubation was about 10% to 20%.^[16,17]^ Ultrasound measurements should predict at least 80% difficulty intubations (Cormack–Lehane grade ≥ 2b), additionally, 20 events are needed to derive two or more correlates in a logistic regression model.^[18]^ It is estimated that a sample size of 106 will be needed, to adjust the possibility 20% of dropout, 127 subjects will be recruited into the study.

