**Inclusion criteria are:**

Patients aged from 18 to 60 years.Live fetus at gestational age ≥ 36 weeks.Singleton or multiple pregnancy.Mentally competent.American Society of Anesthesiologists (ASA) physical status I–III.Subject is planning cesarean section under general anesthesia and tracheal intubation at our maternity at Sichuan Provincial People's Hospital.Informed and written consent.

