**Exclusion criteria are:**

Abnormal pharynx or anatomy.Expected difficult laryngoscopy with cervical spine abnormality, maxillofacial anomalies, upper airway disease, a history of previous difficult intubation.Pregnancies ending with a stillborn.Women presenting for the study but who have been previously included in the study in a previous pregnancy.Women who are unconscious, severely ill, those with learning difficulties, or mentally handicapped.

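### The 10–20% planning incidence comes from obese surgical patients and is not shown to apply to the eligible parturients, although 106 women reach the plan's own 20 events only near the top of that range

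*Protocol article*

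**What the plan says.** All the planning inputs are in section 3.9 (Sample size and study power) of the protocol article. It sets "a statistical power of 80% and a significance level of 0.05 (two-tailed") and then gives its only incidence: "in obese surgical patients, an incidence of difficult intubation was about 10% to 20" per cent. The performance target and event definition follow: "Ultrasound measurements should predict at least 80% difficulty intubations (Cormack–Lehane grade ≥ 2b"). A model requirement is added: "20 events are needed to derive two or more correlates in a logistic regression model". The result is "It is estimated that a sample size of 106 will be needed", raised to 127 recruited for 20% dropout.

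The eligible population is defined in section 3.3. The inclusion list covers age 18–60, gestation of at least 36 weeks, ASA I–III and "Subject is planning cesarean section under general anesthesia and tracheal intubation at our maternity". It has no BMI or obesity threshold; sections 3.4 and 3.5 only record BMI. The exclusion list removes abnormal pharynx or anatomy and "Expected difficult laryngoscopy with cervical spine abnormality, maxillofacial anomalies, upper airway disease, a history of previous difficult intubation".

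Section 3.10 plans a multiple logistic regression for independent predictors and attaches no condition on the number of difficult cases.

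**The concern.** The incidence of the event determines how many difficult cases a study of fixed size will contain. That number governs both the precision of sensitivity and the regression. Here the incidence is taken from a different population (obese surgical patients) and applied to pregnant women of any BMI, some of whom have been screened out for particular airway problems. The document gives no incidence for parturients and no argument that converts one figure into the other. It also does not say whether the source studies used the grade 2b threshold that defines an event here.

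If the incidence in eligible women lies in the lower or middle part of the borrowed range, or below it, the study ends with fewer difficult cases than section 3.9 itself requires. As written, the multivariable model would still be fitted.

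**Working it through.** **Inputs, all from section 3.9:** incidence 10–20%; 20 events required; N = 106 before dropout; 127 recruited; target sensitivity 80%.

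**1. Can 106 be reproduced?** With N = 20 / incidence:
- 10%: 20 / 0.10 = 200
- 15%: 20 / 0.15 = 133.3, so 134
- 20%: 20 / 0.20 = 100

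None of these is 106. Solving backwards, 20 / 106 = 18.9%, which is inside the stated range but not stated. Other routes come close only with inputs the article does not give. Testing an AUC of 0.70 against 0.5 at 20% incidence gives 105. Estimating 80% sensitivity to ±20 percentage points at 15% gives 103. So 18.9% is the incidence at which 106 meets the event requirement, not necessarily the one the authors used. The recruited number does reproduce as 106 × 1.2 = 127.2.

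**2. What 106 delivers.** Expected events = 106 × incidence. The chance of at least 20 events is the binomial upper tail with n = 106. The exact (Clopper–Pearson) 95% interval is for an observed sensitivity as near 80% as whole cases allow. The 5% and 25% rows are assumptions, one on each side of the stated range.

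| Incidence | Expected events | Chance of ≥ 20 events | Example | Exact 95% CI for sensitivity |
|---|---|---|---|---|
| 5% (assumed) | 5.3 | < 0.1% | 4/5 | 28–99% |
| 10% | 10.6 | 0.4% | 9/11 | 48–98% |
| 15% | 15.9 | 16% | 13/16 | 54–96% |
| 20% | 21.2 | 65% | 17/21 | 58–95% |
| 25% (assumed) | 26.5 | 95% | 21/26 | 61–93% |

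**3. Effect of the dropout allowance.** If all 127 women are analysed, 20 events are expected from 20 / 127 = 15.7%, and the chance of at least 20 is 2.8% at 10%, 44% at 15% and 91% at 20%. If the planned 20% is lost, 127 × 0.8 = 101.6 remain and the break-even incidence is 20 / 101.6 = 19.7%. On either count the requirement is not met in expectation over the lower half of the range.

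**4. Does the document link the two populations?** The Abstract and Introduction say parturients have more difficult airways than non-obstetric patients, and the Introduction names obesity among the reasons. No figure is given. The Discussion's comparison with obese patients concerns functional residual capacity and desaturation, not the view at laryngoscopy. These statements make the proxy understandable but supply no incidence.

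**The case against.** The strongest defence is that the proxy is disclosed, cited and reasoned. Pregnancy and obesity share features that make airways harder, and the article says so. That stands: this is a justification gap, not a concealed or absurd input.

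A second defence is that the shortage of events does not depend on the source population. Even if 10–20% were exactly right, 106 women would give 20 events only near the top. That is also true, and it is why the choice of incidence matters: a plan with this little slack needs a figure that belongs to its own patients.

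Three stronger readings are tempting and are not supported:

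- A reader might infer that the borrowed figure measures a different outcome from the study's. Section 3.9 itself applies the term to grade 2b or worse, and the Abstract forms the difficult-intubation group by Cormack–Lehane grade. The definition in the cited studies is not given. All that can be said is that use of the 2b threshold is not shown.
- A reader might infer that the criteria remove all expected difficulty. They remove listed causes and previous difficult intubation. Women with a high Mallampati score, short thyromental distance, large neck or high BMI remain eligible, because these measures are candidate predictors.
- A reader might infer that 10–20% is too high. Women who are not obese, the exclusions, and the withdrawal of unanticipated difficult intubations in section 3.7 would lower the incidence among those analysed. Pregnancy and a threshold as low as 2b could raise it. The document does not settle the balance.

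**Conclusion.** The point holds as a gap in justification. The only incidence behind the sample size comes from obese surgical patients, and the article does not show that it applies to eligible parturients at the grade 2b threshold. The direction of any error is unknown.

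The consequence is that 106 women are expected to yield the required 20 events only at an incidence of about 18.9% or more. Across the plan's own range, the chance of reaching 20 runs from 0.4% to 65%. These figures assume 106 women analysed, independent outcomes and no further loss of events. They use only the plan's stated incidence and event requirement; the 5% and 25% rows are illustrations. The point should be corrected, but it does not show that the study will fall short.

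**What to change.** **Section 3.9.** Replace the borrowed figure with the frequency of Cormack–Lehane grade 2b or worse among women meeting these criteria, from the centre's own records if available. Otherwise present N = 106 over a range extending below 10% and above 20%, with every value outside 10–20% labelled as an assumption. At each value give the expected number of events and the exact confidence interval for 80% sensitivity, as in the table above.

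**Section 3.10.** State that the multivariable model is fitted only if the plan's own requirement of 20 events is met, judged from the Cormack–Lehane grades without reference to the ultrasound data. If it is not met, report the ROC and univariate results as estimates with confidence intervals.

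**Cost.** A records search or a short table, and one added sentence in the analysis section. No extra patients are required. The stated expected precision becomes less favourable, and the independent-predictor analysis may have to be dropped.

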### Laryngoscopy

3.7

When the anesthetic depth was enough, and TOF indicated neuromuscular blockade was deemed as adequate (TOF 1/4 0), the anesthesiologists with more than 5 years of experience perform the laryngoscopy and endotracheal intubation. Patients will be in a standard sniffing position, Macintosh curved laryngoscope blade will be used to perform direct laryngoscopy and intubation. A modified version of the Cormack–Lehane grade will be used to evaluate difficult airway.^[15]^ The Cormack–Lehane grades 1 or 2a will be designated as “easy”, grades 2b or 3a, and grades 3b or 4 represent “restricted or difficult” laryngoscopies: grade 2b (only arytenoids visible), 3a (only epiglottis visible and liftable), 3b (epiglottis adherent to pharynx) and 4 (no laryngeal structures seen). A maximum of three attempts will be permitted. In addition, if the SpO2 decrease to less than 90% or patients with unanticipated difficult ventilation or intubation will be withdrawn from the study. Steps followed the process in the guidelines of the Obstetric Anesthetists’ Association and the Difficult Airway Society will be taken immediately.^[6,14]^ LMA will be utilized to maintain ventilation. If the SGA failed, cricothyroid membrane puncture will be performed immediately. The proper capnograph waveform could confirm the tracheal intubation. The attending anesthesiologist performs the further anesthetic management of the patient.

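### Section 3.9 requires 20 events, but its 106 patients supply 20 expected events only if incidence is at least 18.9%, near the top of the assumed 10–20%

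*Protocol article*

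**What the plan says.** All the sample-size inputs are in section 3.9 (Sample size and study power) of the protocol article:

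- Incidence: "in obese surgical patients, an incidence of difficult intubation was about 10% to 20" per cent. The section does not say which value in that range was used.
- Event requirement: "20 events are needed to derive two or more correlates in a logistic regression model". An event is a Cormack–Lehane grade of 2b or worse.
- Result: "It is estimated that a sample size of 106 will be needed".
- Dropout: "to adjust the possibility 20% of dropout, 127 subjects will be recruited into the study".
- The section also cites 80% power at a two-sided 0.05 level, and a target that "Ultrasound measurements should predict at least 80% difficulty intubations".

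Section 3.7 (Laryngoscopy) adds that "patients with unanticipated difficult ventilation or intubation will be withdrawn from the study". The Discussion acknowledges this withdrawal as a possible source of selection bias. Section 3.10 (Statistics) plans a multiple logistic regression to find independent predictors of difficult intubation.

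**The concern.** The plan sets its own event requirement for the logistic model, and then gives a sample size that meets it only near the top of its own incidence range. This is more than a missing detail: the inputs and the result are both printed, and over most of the range they disagree.

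The multivariable model is meant to identify independent predictors of a difficult airway, which is the subject of the secondary objective. A reader of section 3.9 would take it that 106 patients supply the 20 events that the authors consider necessary. If incidence is in the middle or lower part of the range, the model would be fitted on clearly fewer events than the plan requires, and the plan does not say what would then change.

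**Working it through.** **Inputs, all from section 3.9:** incidence p = 10% to 20%; events required E = 20; evaluable patients N = 106; dropout d = 20%; recruited 127.

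**1. The plan's own figures.** The recruitment figure reproduces as N × (1 + d) = 106 × 1.2 = 127.2, stated as 127. The 106 does not follow from the event requirement at either end of the incidence range: E / p gives 20 / 0.20 = 100 and 20 / 0.10 = 200. It corresponds to 20 / 106 = 18.9%, a value that does not appear in the document.

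**2. Expected events and chance of reaching 20 with 106 evaluable patients.** Expected events = N × p. The chance is the binomial tail P(X ≥ 20 | N = 106, p). Patients needed = 20 / p, rounded up.

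| Incidence | Expected events in 106 | P(at least 20 events) | Patients needed for 20 expected events |
|---|---|---|---|
| 10% | 10.6 | 0.4% | 200 |
| 15% | 15.9 | 16% | 134 |
| 20% | 21.2 | 65% | 100 |

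The requirement is met in expectation only from 18.9% to 20%, about the top tenth of the range: (20 − 18.9) / (20 − 10) ≈ 0.11. Even at 20%, it is missed about one time in three.

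**3. After the planned dropout.** Losing 20% of 127 leaves 127 × 0.8 = 101.6, about 102, which is below the 106 said to be needed. To keep 106 after a 20% loss, recruitment would have to be 106 / 0.8 = 132.5, rounded up to 133. With 101.6 patients the expected events are:

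- at 10%: 101.6 × 0.10 = 10.2
- at 20%: 101.6 × 0.20 = 20.3

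Twenty expected events now need 20 / 101.6 = 19.7%. With 102 evaluable patients, the chance of at least 20 events is 0.2% at 10%, 12% at 15% and 58% at 20%.

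**4. Withdrawals under section 3.7.** Patients with unanticipated difficult intubation leave the study. Such patients are likely to be among those with a grade of 2b or worse, so these withdrawals can take events out of the analysis. The article gives no rate for them and does not say whether the 20% dropout already includes them. No number is attached here; the effect can only lower the event count.

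**5. If nobody is lost.** All 127 patients would give 20 expected events at 20 / 127 = 15.7%. The chance of at least 20 would be 3% at 10% and 44% at 15%.

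**The case against.** The strongest defence is that 20% lies inside the stated range, and at 20% the 106 patients give 21.2 expected events. On that view the plan made an optimistic choice, not an impossible one. This is fair, and it limits the point: the plan relies on the upper end of its range without saying so. The defence does not remove the point, because section 3.9 gives no reason for choosing the upper end, and its own dropout assumption uses up nearly all the margin.

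A second defence is that all 127 patients may be evaluable. That would help, but the plan itself assumes a 20% loss and names 106 as the number needed.

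Four stronger readings are tempting but are not supported by the document:

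- **The 80% power is not delivered.** Section 3.9 ties the power to no null value, effect or test, and an undefined power cannot be shown to be missed. A condensed article may leave those details to a fuller document. Trial calculations also came close to 106 under unstated inputs: for example, a t-test with a standardised difference of 0.9 at 10% incidence needs 108 patients.
- **The true incidence must be lower than 10–20%.** The figure comes from a different population, obese surgical patients, and section 3.3 excludes expected difficult laryngoscopy and previous difficult intubation. The Introduction, however, says that parturients have more difficult airways than non-obstetric patients, and grade 2b counts as an event. The direction of any error is not established.
- **The plan has a rule of one model term per 10 events.** It says only that 20 events are needed for two or more correlates.
- **106 patients give too little precision for sensitivity.** The plan sets no precision target against which this could be judged.

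**Conclusion.** The point stands on the figures in section 3.9 alone. Incidence of 10–20%, a need for 20 events and 106 patients are compatible only from 18.9% incidence upwards. Elsewhere in the range the expected shortfall runs up to 9.4 events (20 − 10.6). On the plan's own dropout assumption the threshold rises to about 19.7%, and 127 recruited patients fall short even of the stated 106.

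The probabilities assume independent patients with a common incidence. The 102 assumes that the planned 20% loss occurs and is unrelated to difficulty; losses concentrated in difficult cases, as section 3.7 allows, would lower the event count further. The conclusion concerns the event requirement of the logistic model. It does not show that the study is underpowered for any particular test, or that 106 is the wrong number for the comparisons in section 3.10.

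**What to change.** Restate section 3.9 along these lines:

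> Recruiting 127 women, with about 102 evaluable after 20% dropout, is expected to yield about 10 to 20 Cormack–Lehane ≥2b events at an incidence of 10–20%. The 20 events needed for the logistic model are expected only at an incidence of about 19.7% or more (18.9% if 106 are evaluable). The incidence is extrapolated from obese surgical patients. If fewer than 20 events are observed, the multivariable model will be limited to fewer terms or reported as exploratory.

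The section should also note that withdrawals under section 3.7 can reduce the number of events, and say whether the 20% dropout includes them. The results should report sensitivity with its exact 95% confidence interval, so that readers can see what the achieved number of events supports.

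The cost is wording only, with no extra patients and no change to endpoints or tests. The price is a less favourable sample-size justification, and possibly a smaller or exploratory multivariable model. The change discloses the shortfall; it does not cure it.

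### Recruiting 127 does not leave 106 after 20% dropout: the allowance was multiplied on (x 1.20) instead of divided out (/ 0.80), leaving about 101 evaluable

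*Protocol article*

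**What the plan says.** The point lies in one sentence of section 3.9 (Sample size and study power) of the protocol article. It first gives the requirement: "It is estimated that a sample size of 106 will be needed". It then gives the recruitment target: "to adjust the possibility 20% of dropout, 127 subjects will be recruited into the study".

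The same section gives the purpose that the number serves. It cites an incidence of difficult intubation of 10% to 20% from earlier work in obese surgical patients, and it states that "20 events are needed to derive two or more correlates in a logistic regression model". No second dropout rate appears anywhere in the article, and neither does a definition of the 20% relative to anything other than the women recruited.

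Section 3.7 (Laryngoscopy) names one route by which women leave the study: "patients with unanticipated difficult ventilation or intubation will be withdrawn from the study". The same sentence also covers a fall in oxygen saturation below 90%.

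**The concern.** A sample size adjusted for dropout should still deliver the required number once the assumed dropout has happened. Here it does not. The recruited figure looks like the required figure plus 20% of itself, which is a different and smaller inflation than one that survives a 20% loss.

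What is at stake is the evaluable number, and through it the count of difficult intubations available for the logistic regression. The section sets a floor of 20 events. Even at the top of its own incidence range there is little slack above that floor, so a few lost women matter more than they would in a study with a comfortable margin.

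**Working it through.** **Inputs, all from section 3.9:** required number 106; dropout 20%; recruited number 127; incidence of difficult intubation 10% to 20%; minimum of 20 events.

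**1. Reproducing the plan's figure.** Adding 20% of the requirement: 106 x (1 + 0.20) = 127.2, reported as 127. The section shows no formula, but this one gives the stated number.

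**2. What 127 delivers at the stated dropout.** 127 x (1 - 0.20) = 101.6, so 101 or 102 women. Against 106 that is 4 to 5 short, or 101.6 / 106 = 95.8% of the requirement.

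**3. What the stated requirement and dropout imply.** 106 / (1 - 0.20) = 132.5, rounded up to 133. The gap to the stated target is 133 - 127 = 6 recruits.

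**4. The dropout that 127 does cover.** 1 - 106 / 127 = 0.165, or 16.5%.

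**5. Consequence for expected events** (evaluable number x incidence):

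| Incidence | 106 evaluable | 101.6 evaluable |
|---|---|---|
| 10% | 10.6 | 10.2 |
| 15% | 15.9 | 15.2 |
| 20% | 21.2 | 20.3 |

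The 15% row is the midpoint of the protocol's range, not a value that it states.

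**6. Consequence for the chance of at least 20 events.** Binomial upper tail, P(X ≥ 20), treating losses as unrelated to outcome. The 101.6 is shown rounded both ways:

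| Incidence | n = 106 | n = 102 | n = 101 |
|---|---|---|---|
| 15% | 16.3% | 12.4% | 11.5% |
| 20% | 65.2% | 57.9% | 55.9% |

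At 10% incidence the chance is below 1% for all three numbers.

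Steps 1 to 4 need only the three figures in the sentence. Steps 5 and 6 describe the size of the effect, and the error does not depend on them.

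**The case against.** The best defence is that the section shows no formula. If the 20% was meant as a margin added on top of 106, then 127 is exactly what that margin gives and nothing is miscalculated. It is true that the multiplication is inferred. But the text calls the 20% dropout, and only a woman who has been recruited can drop out, so its natural base is the recruited number. Nothing in the article defines it otherwise. Even if the margin reading were intended, the text would still promise a protection that 127 does not give.

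The second argument is about weight, and much of it stands. The shortfall is about 4% of the requirement. At 20% incidence the expected events stay just above 20 with either number. At 10% and 15% they miss 20 even with the full 106. So the slip does not decide, in expectation, whether the event floor is met anywhere in the stated range. Whether 106 is large enough for 20 events at the lower incidences is a separate and larger question, which 133 recruits would not settle.

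Two technical cautions also stand. The probabilities move by one to two percentage points according to whether 101.6 is taken as 101 or 102. They also assume that losses are unrelated to outcome, whereas section 3.7 withdraws women with unanticipated difficulty and the Discussion concedes a possible selection bias from this. If losses fall mainly on the difficult cases, more events are lost than the binomial figures show.

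Finally, section 3.9 does not give enough to derive 106 itself. The 133 is therefore right relative to 106, and no independent support for 106 is implied.

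**Conclusion.** The concern holds. The recruitment target does not deliver the number that section 3.9 says is needed at the dropout rate that it assumes: 127 recruited leaves about 101 evaluable at 20% dropout, not 106, and protects 106 only up to 16.5%. This rests on one reading, that dropout is a share of the women recruited, which is the ordinary meaning and the only one that the text supports.

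The error is certain and its effect is modest: about five evaluable women, roughly one expected event at 20% incidence, and a drop of 7 to 9 percentage points in the chance of reaching 20 events at that incidence. It should be corrected because the figure is wrong as written and the correction is easy. On its own it does not undermine the study.

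**What to change.** Correct the sentence in section 3.9 in one of two ways.

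- **Keep 127 and restate what it covers.** Say that 127 recruits retain 106 evaluable women if dropout does not exceed 16.5%, or that at 20% dropout about 101 evaluable women are expected. This costs nothing and changes no design feature.
- **Keep both 106 and 20%.** Change the recruitment target to 133 (106 / 0.80 = 132.5, rounded up). This costs six more recruits at the single site.

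In either case, state that the percentage is a share of the women recruited, so that the allowance can be checked.
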